## Abstract

**Introduction:**

The prevalence of gestational diabetes mellitus (GDM) is rising in the UK. Good glycaemic control improves maternal and neonatal outcomes. Frequent clinical review of patients with GDM by healthcare professionals is required owing to the rapidly changing physiology of pregnancy and its unpredictable course. Novel technologies that allow home blood glucose (BG) monitoring with results transmitted in real time to a healthcare professional have the potential to deliver good-quality healthcare to women more conveniently and at a lower cost to the patient and the healthcare provider compared to the conventional face-to-face or telephone-based consultation. We have developed an integrated GDm-health management system and aim to test the impact of using this system on maternal glycaemic control, costs, patient satisfaction and maternal and neonatal outcomes compared to standard clinic care in a single large publicly funded (National Health Service (NHS)) maternity unit.

**Methods and analysis:**

Women with confirmed gestational diabetes in a current pregnancy are individually randomised to either the GDm-health system and half the normal clinic visits or normal clinic care. Primary outcome is mean BG in each group from recruitment to delivery calculated, with adjustments made for number of BG measurements, proportion of preprandial and postprandial readings and length of time in study, and compared between the groups. The secondary objective will be to compare the two groups for compliance to the allocated BG monitoring regime, maternal and neonatal outcomes, glycaemic control using glycated haemoglobin (HbA1c) and other BG metrics, and patient attitudes to care assessed using a questionnaire and resource use.

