## Methods and analysis

### Objectives

The primary objective of this trial is to evaluate the efficacy of monitoring BG in pregnancy using remote glucose monitoring (GDm-health) compared to standard clinic care. Efficacy will be determined by comparing BG control as determined by mean BG readings from recruitment until delivery between the intervention and the control group. The secondary objective will be to compare the two groups for compliance to the allocated BG monitoring regime, maternal and neonatal outcomes, glycaemic control using glycated haemoglobin (HbA1c) and other BG metrics, and patient attitudes to care assessed using a validated questionnaire^20^ and resource use.

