**Figure 3 BMJOPEN2015009702F3:**
[figure not shown]
Study overview.

BG monitoring targets, dietary advice and thresholds for starting medication will be the same for both allocation groups. All women will be asked to test their BG six times a day on at least 3 days of the week, as per the local guideline. This consists of a fasting sample, 1 h post breakfast, pre-lunch, 1 h post lunch, pre-dinner and 1 h post dinner. Optimal BG is a fasting reading ≥3.5 and ≤5.8 mmol/L and 1 h postprandial readings below 7.8 mmol/L.^11^ If there are persistently high BG readings, or medication is deemed to be required, women will be asked to increase monitoring to 7 days/week.

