**Figure 4 BMJOPEN2015009702F4:**
[figure not shown]
The GDm-health Management System.

Participants will be invited to contact the specialist diabetic midwife using a call-back request function in the smartphone application, or by phone call, if they have any concerns. A specialist diabetes midwife will review the results of the remote monitoring at least three times a week. If a participant has two or more consecutive postprandial readings ≥7.8 mmol/L or fasting readings ≥5.9 mmol/L or one reading above 9.0 mmol/L at any time of day, the specialist midwife will call the participant or send an SMS message from the web interface to the participant’'s phone inviting discussion and further dietary advice. If fewer than 12 of the minimum 18 readings a week are being done, an automatic alert will be generated on the web interface for the diabetes specialist midwife. If this alert persists for 2 weeks, the specialist diabetes midwife will contact the participant. If there is evidence that pharmacological treatment is required, the participant will be referred to the consultant-led clinic to start treatment. Further dose adjustments and messages of advice/encouragement will be communicated to the participant between clinic visits via the GDm-health management system by the specialist diabetes midwife.

Measures taken in both groups at subsequent visits and after delivery are listed in box 1.

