### Analysis of end points

#### Primary end point analyses

The primary end points will be efficacy of the GDm-health system to achieve glycaemic control compared between groups. The results will be reported as a comparison between the two groups of change over time of BG level. The complete data form a complex longitudinal data set, over gestational age. A mixed-model analysis will be carried out on the data of the glucose level. The BG is measured six times per day according to the prescribed schedule, and levels of the multilevel analysis will be time point, gestational age and patient. In addition to the repeated measurements of BG, patient covariates (age, body mass index (BMI), gestation at recruitment, ethnic group) will be included in the model as fixed effects.

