Gestational age at delivery (and percentage of deliveries before 37 weeks);Birth weight (and percentage of babies with birth weight above 90th centile as per the INTERGROWTH-21st Standards for gestational age and gender);Mode of delivery (vaginal, caesarean, assisted);Perineal trauma (third-degree or fourth-degree perineal tear or tear requiring suturing in the operating room);Incidence of shoulder dystocia/birth injury;Incidence of neonatal hypoglycaemia (defined as a serum BG level of <1.5 mmol/L at any time, or requiring special care baby unit (SCBU) admission for feeding);Incidence of neonatal significant hyperbilirubinaemia (defined as requiring phototherapy indicated by a serum bilirubin level of >200 μmol/L at <35 weeks, >250 μmol/L at 35–36 weeks and >300 μmol/L at ≥37 weeks);Maternal weight gain (adjusted for weeks in trial);Maternal pregnancy-induced hypertension or pre-eclampsia (defined according to the International Society for the Study of Hypertension in Pregnancy (ISSHP) criteria^23^);Admission to higher level of care for mother;Admission to higher level of care for neonate.

*Maternal and neonatal outcome analysis*: An analysis of covariance will be carried out when the outcome variable is continuous. The model will contain the term for randomisation group and baseline covariates. The results of a comparison between the two groups will be reported as a treatment effect with 95% CI. The binary variables will be analysed using logistic regression. The model will contain a term for randomisation group and baseline covariates. The results of a comparison between the two groups will be reported as an OR and a risk difference with 95% CI.

*Participants' attitudes*
Patients' attitudes will be assessed by completion of the Oxford Maternity Diabetes Satisfaction survey. This survey was developed based on several existing satisfaction surveys for diabetes management and was adapted and validated within this population.^20^ Descriptive analysis of the scores will be presented and thematic analysis of free-text comments performed.

*Compliance with the BG monitoring system*: Summary statistics will be calculated to describe the frequency of BG measurements.

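### The abstract and the methods state different adjustments for the primary mean BG comparison; the abstract's version uses post-randomisation variables and can bias the contrast

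*Protocol article*

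**What the plan says.** Two parts of the protocol article describe how the primary comparison is adjusted.

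- **Abstract, Methods and analysis.** The primary outcome is each arm's average BG over the whole of participation, and the abstract's stated handling of it is "with adjustments made for number of BG measurements, proportion of preprandial and postprandial readings and length of time in study".
- **Primary end point analyses.** A mixed model is fitted to the glucose readings. Its structure is "levels of the multilevel analysis will be time point, gestational age and patient", and "patient covariates (age, body mass index (BMI), gestation at recruitment, ethnic group) will be included in the model as fixed effects". None of the abstract's three adjusters is in this list.

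Other sections show where those adjusters come from.

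- **Treatment allocation.** Both arms test six times a day on at least 3 days a week. If readings are persistently high, or medication is thought necessary, "women will be asked to increase monitoring to 7 days/week".
- **Remote glucose monitoring group.** "If fewer than 12 of the minimum 18 readings a week are being done, an automatic alert will be generated"; if the alert lasts 2 weeks, the midwife makes contact. The section on the standard clinic care group describes nothing similar.
- **Objectives.** A secondary aim is to "compare the two groups for compliance to the allocated BG monitoring regime".
- **Study design.** Participation runs from recruitment to delivery. The secondary end points include "Gestational age at delivery (and percentage of deliveries before 37 weeks").

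**The concern.** A reader cannot tell which adjustment defines the primary result, and the choice matters. Covariates fixed before randomisation leave the comparison of arms intact. Covariates formed afterwards need not.

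Number of readings is the clearest case. The protocol makes it depend on the outcome (high BG leads to denser testing) and gives a route by which it may depend on the arm (the low-count alert). A variable influenced by both allocation and outcome is a collider. Comparing women with equal counts then compares unlike women across arms, and a difference can appear where none exists. If the count depends on BG only, conditioning on it removes part of a true effect.

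Length of time in study has a baseline part, gestation at recruitment, which is already a covariate in the methods. What it adds is the time of delivery, which is known only after randomisation and is itself an outcome.

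**Working it through.** **1. The plan's own figure.** Inputs from Sample size: SD 0.8 mmol/L, 100 per arm, 80% power, significance level 0.05 (taken as two-sided).

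Detectable difference = (1.960 + 0.842) × 0.8 × √(2/100) = 0.317, or 0.319 with the t distribution. The stated 0.32 reproduces; power at 0.32 is 80.7% (normal) or 80.4% (t). This point does not affect the sample size.

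**2. How far BG can move the count.** From Treatment allocation: 6 × 3 = 18 readings a week at the minimum and 6 × 7 = 42 after escalation. The ratio is 42/18 = 2.3.

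**3. Effect of entering the count as a woman-level covariate.** Define:

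- τ: true arm difference in mean BG (intervention minus control)
- ρ: within-arm correlation between count and mean BG
- d: direct effect of arm on the count, in SDs of the count
- D = d + ρτ/SD: total arm difference in the count, including the part carried by BG

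The within-arm slope of BG on the standardised count is ρ × SD, so

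adjusted difference = τ − ρ × SD × D.

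The documents give neither ρ nor d. Assumed ranges: ρ from 0 to 0.5, d from 0 to 0.5.

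**4. No true effect (τ = 0).** The shift is −ρ × 0.8 × d. Type I error is from 2,000 simulated trials per cell, 100 per arm.

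| ρ | d | Shift (mmol/L) | Type I error |
|---|---|---|---|
| 0 | 0.5 | 0 | 5.7% |
| 0.1 | 0.25 | -0.02 | 5.4% |
| 0.3 | 0 | 0 | 5.5% |
| 0.3 | 0.25 | -0.06 | 9.7% |
| 0.3 | 0.5 | -0.12 | 18.8% |
| 0.5 | 0 | 0 | 4.4% |
| 0.5 | 0.25 | -0.10 | 17.8% |
| 0.5 | 0.5 | -0.20 | 50.0% |

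Without the covariate, the mean difference was about 0 in every cell. The largest shift is 0.20/0.32 = 63% of the design difference. The sign follows ρ × d: if women who test more were better controlled, say ρ = -0.3 with d = 0.5, the shift would be −(−0.3) × 0.8 × 0.5 = +0.12, against the intervention.

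**5. True effect τ = -0.32, count driven by BG only (d = 0).** The formula reduces to τ(1 − ρ²).

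- ρ = 0.3: -0.32 × 0.91 = -0.29
- ρ = 0.5: -0.32 × 0.75 = -0.24; simulated power is about 68%, against the planned 80%

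**6. Why uneven sampling still needs handling.** Take a woman with 5 weeks at 18 readings (mean 6.0) and 5 weeks at 42 readings (mean 6.5); these BG values are illustrative. Averaging all readings gives (90 × 6.0 + 210 × 6.5)/300 = 6.35. Weighting weeks equally gives 6.25. So dropping the count as a covariate is not the whole remedy: the weighting of weeks must be stated as well.

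**The case against.** The strongest reply is that the adjustment appears only in the abstract, whereas the methods section sets out a sound model with baseline covariates. On this reading the abstract is loose shorthand for that model. The HbA1c text supports it: there, a varying number of measurements is something the mixed model takes into account, not a covariate. Sample size likewise sets the multilevel analysis apart from a plain mean of all readings. This much stands: the abstract does not say that its adjusters are covariates, so bias is conditional on that reading. But the methods do not withdraw the abstract's wording, and that wording is attached to the primary outcome.

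A reader might infer more than the document supports.

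- **That arm or BG drives all three adjusters.** Both arms follow the same six-point schedule, and nothing shows an effect of either on the pre/postprandial mix. Standardising for reading type at reading level is legitimate.
- **That allocation changes time in study.** No section says it alters delivery timing. Listing gestational age at delivery as an outcome does not show an effect.
- **That false-positive rates will be very high.** Rates of 54% and 86% can be generated with 4 and 6 extra readings a week and a within-arm correlation of about 0.52. Neither input is in the document. At a correlation of 0.30 the same increments give 18% and 35%; at 0.16, 9% and 14%; with no dependence on BG, about 5%.
- **That the alert clearly raises the count.** It fires only below 12 readings a week and leads to contact only after 2 weeks. The route is plausible, but its size is unknown.

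**Conclusion.** The inconsistency is plain: abstract and methods adjust the primary comparison differently. The risk of bias is real but conditional. It arises if number of readings or time in study enters the primary model as a woman-level covariate. It is best supported for number of readings, where the protocol documents the link to BG and describes an alert for one arm only.

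The size cannot be fixed from the document. Over the assumed ranges, and with no true effect, it runs from nothing to about -0.20 mmol/L. Where BG alone drives the count, a true effect is understated by roughly 0.03 to 0.08 mmol/L. These figures come from a woman-level regression, not from the mixed model in the methods, which would avoid the problem if used as written. The document does not support saying that the primary result is biased as planned; it supports saying that one of its two stated adjustments could make it so.

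**What to change.** Amend the abstract to match the primary end point analyses, and make clear that the following is the primary analysis.

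- Leave number of readings and length of time in study out of the primary intention-to-treat model. If they are of interest, use them in a labelled sensitivity analysis at most.
- Keep baseline covariates only. Gestation at recruitment already carries the baseline part of time in study.
- Replace the woman-level pre/postprandial proportion with the six scheduled time points, modelled at reading level together with gestational age.
- Report the arm difference standardised over time points and weeks, so that densely sampled weeks of poor control are not over-weighted.

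The cost is protocol wording and analysis code. No patients, visits or data are added, and the sample size is unchanged.

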**Ethics and dissemination:**

Thresholds for treatment, dietary advice and clinical management are the same in both groups. The results of the study will be published in a peer-reviewed journal and disseminated electronically and in print.

**Trial registration number:**

NCT01916694; Pre-results.

Strengths and limitations of this studyThis will be the most rigorous and robust evaluation of an integrated telehealth solution for the gestational diabetes population to date.The intervention has been developed and piloted prior to the study with input from consumer groups: patients, clinicians and biomedical engineers.This study will be conducted within the maternity diabetes service of a National Health Service (NHS) hospital, therefore capturing data in a ‘real-life’ scenario.As adverse clinical outcomes such as shoulder dystocia, birth trauma or stillbirth are relatively uncommon in women with gestational diabetes mellitus receiving treatment, this study will not be able to be powered on these outcomes.The optimal metric for measuring glycaemic control in the gestational diabetic population is not known. We plan to assess the difference in overall mean blood glucose between the two groups as the primary outcome for this trial; however, an intended objective will also be to assess and compare other summative metrics of glucose control. This will enable us to select a valid primary outcome measure, with known SD and estimation of effect size, to allow calculation of sample size for a future definitive trial.The study will be conducted in a single UK tertiary centre where women have high rates of literacy and relatively low levels of social deprivation; therefore, further evaluation will be needed to demonstrate effectiveness in other settings.

## Introduction

Gestational diabetes mellitus (GDM) is defined by the WHO as ‘carbohydrate intolerance resulting in hyperglycaemia of variable severity with onset or first recognition during pregnancy’.^1^ Maternal hyperglycaemia leads to excess transfer of glucose to the fetus resulting in fetal hyperinsulinaemia. The consequence of this is accelerated fetal growth and large babies, which increases the risk of delivery complications such as shoulder dystocia, birth trauma, the need for caesarean section and increased risk of stillbirth.^2^ Recognising and treating gestational diabetes to achieve tight glycaemic control has been shown in randomised controlled trials to reduce obstetric and fetal complications.^3^
^4^

Blood glucose (BG) metabolism and regulation change rapidly in pregnancy. The development of GDM and its progression to requiring pharmacologic treatment can be difficult to predict accurately. Once a woman is on insulin treatment, rapid upward titration of insulin dose is commonly required to maintain optimal glycaemic control and rarely hypoglycaemic episodes may require reduction in insulin dosages.

In order to detect and respond to these physiological and metabolic changes, women with GDM are commonly reviewed by a hospital-based maternity diabetes team, at frequent and regular intervals—typically every 1–4 weeks. This constitutes a significant burden to the patient of having to attend many additional antenatal clinics and to the health system responsible for care.

In recent years, there has been a widening of GDM screening criteria,^5^ a lowering of diagnostic thresholds,^6^ an increasing proportion of pregnant women who are classed overweight or obese and increasing numbers of women from high-risk ethnic groups. These changes have led to a rise in the prevalence of GDM, from a baseline of around 4% in 2008^5^ predicted to reach over 16% in the UK if the new diagnostic thresholds are widely adopted.^7^ Taking these factors together, current maternity diabetes services are likely to become overwhelmed and provision and funding will be required for rapid expansion of these services.

The concept of women being able to monitor their BG levels at home with results transmitted in real time to a healthcare provider with bidirectional communication is attractive. Technology intended to deliver healthcare at a distance using an electronic means of communication is referred to as digital health. M-health is a subcategory of digital health where smartphones are used to transfer data and run applications to integrate with other health technology and services.

We developed a novel m-health management system for women with GDM (GDm-health). This system was designed to be an intuitive, interactive, reliable and accurate digital health solution for women with GDM.^8^ GDm-health was designed to include a smartphone application for the patients and a web interface for the clinicians. It incorporates several features of digital health technology that have only been evaluated in isolation before, including bidirectional communication, integration with an existing health system and digital recording and analysis of BG results. The system was developed in collaboration with women with GDM, healthcare professionals and biomedical engineers to create a system that could potentially be fully integrated into routine clinical care within the National Health Service (NHS), with an interface that was easy to use for staff and patients. Full details of development of the system are provided elsewhere.^8^ Additionally, the system needed to be fully secure, low cost and based on readily available technologies. It is this system that we are using to compare remote BG monitoring with standard clinic care in the gestational diabetic population.

The evidence base for m-health as an intervention to improve glycaemic control in diabetes outside pregnancy is becoming increasingly well established.^9^ Our team members have had experience with developing and evaluating solutions for the management of type 1 and 2 diabetes using these approaches.^10–12^

There are few published studies of digital health solutions for the management of women with GDM. Most have enrolled only small numbers of women and have been conducted with methodological approaches at risk of bias. Comparison is hampered by the wide range of technologies that have been developed, with little agreement on the key components of interventions, the appropriate comparator group(s) or primary outcome measures.

Consequently, the true effects and possible benefits or harms of digital health solutions on GDM are not understood. While four studies of women with GDM (272 women) failed to demonstrate any impact on pregnancy outcomes or glycaemic control,^13–16^ other studies of women with type 1 diabetes^17–19^ or GDM^19^ showed an association with better glycaemic control and improved outcomes in the digital health group compared to standard care. It has been proposed that the value of telehealth solutions may be in reducing the number of outpatient clinic visits required,^16^ and there is evidence of improved satisfaction with care among patients and healthcare professionals.^13^
^14^
^19^ Sustainability and scale up of the technologies has proven challenging, with no examples in the published literature describing successful widespread implementation and adoption beyond the research setting of telehealth solutions for GDM.

## Methods and analysis

### Objectives

The primary objective of this trial is to evaluate the efficacy of monitoring BG in pregnancy using remote glucose monitoring (GDm-health) compared to standard clinic care. Efficacy will be determined by comparing BG control as determined by mean BG readings from recruitment until delivery between the intervention and the control group. The secondary objective will be to compare the two groups for compliance to the allocated BG monitoring regime, maternal and neonatal outcomes, glycaemic control using glycated haemoglobin (HbA1c) and other BG metrics, and patient attitudes to care assessed using a validated questionnaire^20^ and resource use.

